### 9.1 Primary study parameter(s)

The primary endpoint is an assessment of the difference between the two treatment groups in the volume (in liters) of IV fluid resuscitation at three hours (excluding prehospital fluids).. Statistical analysis will be conducted to compare baseline characteristics and outcomes between the study arms. Non-normally distributed data will be analyzed using the Mann-Whitney U test, while normally distributed data will be analyzed using an independent samples Student's t-test. A p-value of  $<0.05$  will be considered significant.

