## 2. OBJECTIVES

### Primary Objective:

The primary objective is to assess the effect of the personalized hemodynamic resuscitation protocol guided by the Starling SV monitor on the volume (in liters) of intravenous (IV) fluid resuscitation within the first three hours of their emergency department (ED) admission.

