#### 4.4 Sample size calculation

##### Estimated sample size

Sample size was calculated using R (version 4.3.1), based on data from a comparable study with similar methodology and endpoint definitions (14). That reference study demonstrated a mean difference of 1.37 L in positive fluid balance at 72 hours between groups, with the intervention group showing  $0.65 \pm 2.85$  L compared to  $2.02 \pm 3.44$  L in the control group (14). The effect size (Cohen's  $d = 0.45$ ) was calculated from the reported means and standard deviations.

We conducted an a priori power analysis via a Monte Carlo simulation (50,000 replicates) assuming normal distributions for each arm with observed means and standard deviations. To accommodate unequal variances, a two-tailed Welch's t-test ( $\alpha = 0.05$ ) was applied in the simulated dataset. The simulation showed that 170 participants (85 per group) are needed to achieve 80% power to detect a statistically significant difference in the primary endpoint (IV fluid volume administered within the first three hours after study enrollment). Anticipating 10% drop-out due to loss to follow-up, study withdrawal, or protocol deviations, the total planned sample size is 188 participants (94 per group).

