| Demographic data (i.e. age, sex, ethnicity, length, weight, BMI)                                                       |               | x               |                  |            |           |            |
| Medication use (i.e. cardiovascular, immunosuppressiva, diuretics)                                                     |               | x               | x                | x          |           |            |
| Co-morbidity (pre-existent, developing)                                                                                | x             |                 | x                | x          | x         | x          |
| Mortality (in-hospital, out-of-hospital)                                                                               |               |                 | x                | x          | x         | x          |
| Hospital admission (i.e. general ward, ICU)                                                                            |               | x               | x                | x          | x         | x          |
| Disease severity scores (i.e. SIRS, [q]SOFA, NEWS)                                                                     | x             | x               | x                | x          | x**       |            |
| Vital parameters (i.e. SBP, DBP, heart rate, respiratory rate, SpO2, temperature, GCS, CRT)                            | x             | x               | x                | x          |           |            |
| Lab values (i.e. leukocytes (including machine differential), thrombocytes, creatinin, bilirubin, CRP, albumin, ureum) | x             |                 | x                | x          | x         |            |
| Extended lab values (i.e. pH, lactate, NT-proBNP)                                                                      | x             |                 | x                |            |           |            |
| Organ support information (i.e. hemodynamic support, RRT, [non-]invasive mechanical ventilation, ECMO)                 | x             | x               | x                | x          | x         | x          |
| Volume of IV fluids (time, amount, type)                                                                               | x             | x               | x                | x          |           |            |

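### Section 9.1 lets the observed distribution choose between two primary tests; neither is the Welch test behind the sample size, and no between-arm difference in litres is fixed

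*Protocol*

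**What the plan says.** - **Question.** Protocol section 2 asks for the effect of the guided protocol "on the volume (in liters) of intravenous (IV) fluid resuscitation within the first three hours". Section 9.1 opens: "The primary endpoint is an assessment of the difference between the two treatment groups in the volume (in liters) of IV fluid resuscitation". The time point there is three hours, and prehospital fluid is left out.
- **Test.** Section 9.1 continues: "Non-normally distributed data will be analyzed using the Mann-Whitney U test, while normally distributed data will be analyzed using an independent samples". The second test is Student's t-test, and significance is set at p<0.05. The section does not say how normality is judged, and it names no between-arm estimate.
- **Sample size.** Section 4.4 simulates the trial "assuming normal distributions for each arm with observed means and standard deviations" and states: "To accommodate unequal variances, a two-tailed Welch's t-test". Its target is a mean difference of 1.37 L, which needs 85 per group.
- **Descriptive summaries.** The introduction to chapter 9 lists means, medians, standard deviations and confidence intervals for continuous variables. It does not commit to an interval for the difference between arms.
- **What is deferred.** Section 9.2 leaves a later plan only for binary and time-to-event secondary endpoints. It repeats the same two-test rule for the others.

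**The concern.** Three parts of the protocol point to different analyses. The sample size targets a mean difference in litres by Welch's test. The primary analysis is either Student's t-test or a rank test, and the outcome data decide which, by an unstated criterion. The trial is also open-label, so this leaves avoidable discretion over the primary p-value.

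The choice matters because the two tests answer different questions. The t-test compares mean litres. Mann-Whitney asks whether a patient in one arm tends to have a larger volume than a patient in the other. Section 5.1 directs further boluses to responders and withholds them from many non-responders, so a change in the shape of the distribution is an expected effect of guidance. In that case a significant rank test could be reported as less fluid while mean litres are the same, with no planned between-arm interval to show it.

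**Working it through.** **1. Reproduce the protocol's sample size.** Inputs from section 4.4: 0.65 (SD 2.85) L against 2.02 (SD 3.44) L, two-sided alpha 0.05, power 80%.
- Pooled SD = √((2.85² + 3.44²)/2) = √((8.1225 + 11.8336)/2) = 3.159 L.
- Standardised difference = 1.37/3.159 = 0.434.
- n per arm = 2(1.960 + 0.842)²/0.434² ≈ 84 by the normal approximation.
- Welch simulation, 50,000 replicates: power 0.799 at 84 per arm and 0.803 at 85.

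The stated 85 per group is reproduced. (The printed effect size of 0.45 would need about 78 per arm; the sample size fits 0.434.)

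**2. Put the section 9.1 tests on the same normal inputs, 85 per arm.**

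| Test | Power |
|---|---|
| Welch (section 4.4) | 0.803 |
| Student (section 9.1) | 0.803 |
| Mann-Whitney (section 9.1) | 0.776 |

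With equal arms, Student against Welch makes no practical difference. Mann-Whitney costs 2 to 3 percentage points.

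**3. Which test will the rule select?** Section 5.1 gives guided fluid in 500 mL boluses, and section 3 gives every patient in both arms a first bolus. Volumes are therefore likely to be lumpy with a floor. Taking Shapiro-Wilk as the check (an assumption), simulated volumes in 0.5 L steps were rejected in 100% of trials. With continuous noise of SD 0.1 to 0.3 L added, they were rejected in 99% to 100%.

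**4. Equal mean volumes, different shapes.** All distributions are assumed, because the protocol gives none for three-hour volume. Bolus counts are Poisson-type in 0.5 L steps unless stated. In the split scenarios (94 per arm) both means are 2.0 L; for example, 60% × 1.0 + 40% × 3.5 = 2.0. The entries are the share of trials with p<0.05.

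| Scenario | Mann-Whitney | Welch |
|---|---|---|
| Guided 50/50 at 1.5/2.5 L, at least one bolus each | 6% | about 5% |
| Guided 60/40 at 1.5/2.75 L, at least one bolus each | 7% | about 5% |
| Guided 50/50 at 1.25/2.75 L, at least one bolus each | 9–10% | about 5% |
| Both means 1.50 L, SD 1.08 (control) against 0.71 (guided), 85 per arm | 21.7% | 4.6% |
| Guided 60/40 at 1.0/3.5 L, zero boluses allowed | 22% | about 5% |
| Guided 60/40 at 1.0/3.5 L, at least one bolus each | 37–40% | about 5% |
| Guided 60/40 at exactly 1.0/3.5 L, control tightly clustered at 2.0 L (normal, SD 0.5 L, rounded to 0.5 L) | 50% | about 5% |

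When both arms have the same distribution, the two-step rule rejects in 4.95% of trials.

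**5. When guidance lowers the mean.** With means of 1.5 against 1.1 L in 0.5 L steps, 85 per arm, power was 0.74 for Mann-Whitney against 0.82 for Welch with the most skewed data, and 0.96 against 0.97 with the least skewed.

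**6. Optional covariates.** Section 8.3, Table 1 already collects "Demographic data (i.e. age, sex, ethnicity, length, weight, BMI") at baseline, and vital signs and lactate at triage. If covariates explain a share R² of the variance, the standardised difference becomes 0.434/√(1 − R²). Power at 85 per arm is 80% with R² = 0, and 84%, 88% and 92% with R² = 0.1, 0.2 and 0.3. The documents give no R², so this range is assumed. It also borrows the 72-hour fluid-balance inputs of section 4.4.

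**The case against.** Several points on the other side stand.

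- Sections 2 and 9.1 speak of volume in litres and of a difference, but neither says mean; only section 4.4 does. A rank test of whether guided patients tend to receive less fluid is a defensible reading of the objective. It does not match the quantity on which the trial was sized.
- A reader might infer that the primary test is certain to be Mann-Whitney. The protocol does not support that. Section 9.1 names no formal normality test, the 500 mL step is fixed only for the guided arm, and control treatment is at the physician's discretion.
- A reader might infer that the trial will report nothing in litres. Chapter 9 promises summaries of continuous variables, so litres per arm should appear. What is missing is the between-arm difference with its interval.
- A reader might infer that the false-positive rate is inflated in general, or that 50% is typical. Neither follows. The rule keeps its level under identical distributions, and 50% comes from one extreme scenario while milder ones stay near 5%. Under a simple reduction from 2.0 to 1.6 L, one simulation gave 92% power for Mann-Whitney and 93% for Welch.
- An unadjusted comparison in a randomised trial is valid, and covariates may be left to an analysis plan. Leaving them out of section 9.1 is not an error.

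An unseen analysis plan does not settle the main point. Section 9.1 states the two-test rule outright for the primary endpoint, and section 9.2 defers only other analyses.

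**Conclusion.** The point holds in a limited form. Section 9.1 fixes a data-dependent choice between two tests by an unstated criterion, differs from the Welch test in section 4.4, and commits to no between-arm estimate in litres. The trial remains valid, but its primary analysis may not estimate what it was powered for.

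On the protocol's own normal inputs the cost is small: about 78% power for Mann-Whitney against 80% for Welch, and nothing for Student against Welch. The larger risk is interpretive. With equal mean volumes but different shapes, Mann-Whitney rejected in about 5% to 50% of simulated trials against about 5% for Welch. That range rests wholly on assumed distributions, and neither end is a bound. That Mann-Whitney will be selected is likely but remains an inference. Covariate adjustment is an optional gain in precision whose size depends on an unknown R².

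**What to change.** In section 9.1, delete the normality-based choice and pre-specify one primary analysis consistent with section 4.4: the difference in mean three-hour IV fluid volume in litres, with a 95% CI, by Welch's method or by a linear model on arm with heteroscedasticity-robust standard errors, whatever the observed distribution. Keep Mann-Whitney as a sensitivity analysis only. Section 9.2 should follow the same principle for continuous secondary endpoints.

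Optional: adjust the linear model for named baseline variables that are already collected and not affected by allocation, such as body weight, triage MAP or shock index, and triage lactate. Confirm that the triage values are recorded before study treatment starts. Do not use ED fluid before randomisation as a covariate: section 8.2 lets randomisation begin before arrival, so that quantity may be zero or undefined for many patients.

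The cost is one paragraph of text, fixed before outcome data are examined. It needs no new data and no change to the sample size.

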### 9.2 Secondary study parameter(s)

Secondary endpoints are included in statistical analysis regardless of the outcome of the primary endpoint . Similar to the primary analysis, differences between the study groups will be analyzed using the Mann-Whitney U test for non-normally distributed data and an independent samples Student's t-test for normally distributed data. A p-value of  $<0.05$  will be considered significant.

For binary and time-to-event analyses concerning secondary study parameters, a detailed analysis plan will be developed and finalized in a timely manner.

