### Secondary Objective(s):

#### Efficacy

- To assess the effect of the personalized hemodynamic resuscitation protocol guided by the Starling SV monitor on the initiation of vasopressor therapy, measured in time, within the first three hours of their ED admission.
- To evaluate the effect of the personalized hemodynamic resuscitation protocol guided by the Starling SV monitor in guiding hemodynamic resuscitation on organ dysfunction scores within 48 hours.
- To compare fluid balance (in litres) within three hours between the sepsis patient group receiving hemodynamic resuscitation guided by the Starling SV monitor and the group receiving standard care.
- To assess the impact of the use of a personalized hemodynamic resuscitation protocol on the length-of-stay in the hospital for sepsis patients admitted to the ED.
- To evaluate the effect of the use of a personalized hemodynamic resuscitation protocol on the 7-day and 30-day mortality rate of sepsis patients.
- To assess the amount of fluid administered within the first three hours of their ED admission between the fluid responder group and the fluid non-responder group.

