#### 8.1.2 Secondary study parameters/endpoints

##### **Efficacy**

|                           |                                                                                                                                                                                                                                                                                                                                                                                               |
|---------------------------|-----------------------------------------------------------------------------------------------------------------------------------------------------------------------------------------------------------------------------------------------------------------------------------------------------------------------------------------------------------------------------------------------|
| Hospital admission        | 
 
Length-of-stay in hospital
 
ICU admission within 7 days (excluding subjects receiving protocolized vasopressor therapy)
 
                                                                                                                                                                                                             |
| New onset organ failure   | Any of the following within 48 hours: 
 
Rise in SOFA score of at least 2
 
Organ support (i.e. vasopressor use [non-]invasive mechanical ventilation, acute dialysis, ECMO)
 
                                                                                                                                                            |
| Fluid resuscitation       | 
 
Volume of IV fluid resuscitation within three hours (including prehospital fluids administered)
 
Volume of IV fluid resuscitation within 7 days
 
Fluid balance within three hours (i.e difference between volume of intravenous plus oral fluids and the volume of fluid output (i.e. urine output and other fluid losses))
 
 |

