| Vasopressor therapy                | 
 
• Vasopressor therapy within three hours
 
• Vasopressor therapy within 7 days
 
• Time to vasopressor therapy
 
                                                                                                                                                                                                                                                                                                                   |
| All-cause mortality                | 
 
• Mortality within 48 hours
 
• In-hospital mortality
 
• Mortality within 30 days
 
                                                                                                                                                                                                                                                                                                                                               |

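### Section 9.2 calls unadjusted p < 0.05 significant for secondary endpoints whatever the primary shows, with no hierarchy or supportive status; for the 6 continuous secondaries it fixes, that is about a 21% chance of a false claim

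*Protocol*

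**What the plan says.** Section 9.2 makes three statements about the secondaries.

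- They do not depend on the primary: "Secondary endpoints are included in statistical analysis regardless of the outcome of the primary endpoint".
- For the tests, "differences between the study groups will be analyzed using the Mann-Whitney U test for non-normally distributed data and an independent samples Student's t-test". The t-test is the choice where the data look normal. The same paragraph ends by saying that a p-value below 0.05 "will be considered significant".
- A separate paragraph then defers the rest: "For binary and time-to-event analyses concerning secondary study parameters, a detailed analysis plan will be developed and finalized in a timely manner".

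Section 8.1.2 lists the endpoints in efficacy, safety, health-technology and exploratory mechanistic blocks. Only the mechanistic block carries the word exploratory. No ranking, alpha allocation or adjustment appears for the efficacy and safety blocks.

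Three neighbouring statements bear on the same rule.

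- Section 2 has, as an efficacy objective, the effect "on the 7-day and 30-day mortality rate of sepsis patients". Section 8.1.2 puts mortality under safety, at other times: "Mortality within 48 hours", in hospital, and 30 days.
- Time to starting vasopressors is an efficacy objective in section 2 and a safety endpoint in 8.1.2.
- Section 9.1 says "Statistical analysis will be conducted to compare baseline characteristics and outcomes between the study arms", and the tests and the 0.05 threshold that follow apply to both.

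**The concern.** The primary is one contrast with one test, and its error rate is not in question. The difficulty is what may be said about the secondaries. Analysing them after a negative primary is reasonable. Calling each one significant at an unadjusted 0.05, with nothing to mark it as supportive, is a different matter. Labelling only the mechanistic block exploratory invites the reading that the other secondaries are not.

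This matters more than usual here because the primary, litres of fluid given in three hours, is a process measure. A statement about patient benefit has to come from a secondary. Among the secondaries whose test and threshold are already fixed, the one of that kind is "Length-of-stay in hospital". As written, the trial could miss its primary and still report an isolated length-of-stay result as significant.

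The mismatch between sections 2 and 8.1.2 adds to this: it is not settled which mortality times count, or whether time to vasopressor would be claimed as efficacy.

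**Working it through.** **The plan's own figure.** The protocol states no family-wise error rate for the secondaries, so there is none to reproduce. The level is 0.05 (9.2). Section 9.2 does not give sidedness; two-sided is taken from the power calculation in 4.4.

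**Step 1: count the endpoints in 8.1.2**, with each composite counted once and repeat time points within one item not split.

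| Block | Continuous | Time-to-event | Binary | Total |
|---|---|---|---|---|
| Efficacy | 4 | 1 | 3 | 8 |
| Safety | 2 | 1 | 15 | 18 |
| Both | 6 | 2 | 18 | 26 |

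The 4 continuous efficacy items are length of stay, IV volume at three hours including prehospital fluid, IV volume to 7 days, and fluid balance at three hours. The 2 continuous safety items are the creatinine changes to 48 hours and to day 7. The time-to-event items are time to hemodynamic stability and time to vasopressor.

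**Step 2: decide which endpoints the rule covers.** The 0.05 sentence closes the paragraph on Mann-Whitney and t-tests, which fits the 6 continuous items. The other 2 + 18 = 20 fall in the deferred group.

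**Step 3: chance of at least one false significant result when no endpoint is truly affected.** The protocol gives no correlation between endpoints, so a common correlation ρ is assumed, with 0.5 as the central value and 0.8 to 0 as the range.

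- For independent tests: 1 − 0.95^k.
- For equal correlation ρ, with c = 1.96: 1 − ∫ [Φ((c − √ρ·z)/√(1−ρ)) − Φ((−c − √ρ·z)/√(1−ρ))]^k φ(z) dz, evaluated numerically.

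| Family | k | ρ = 0 | ρ = 0.5 | ρ = 0.8 |
|---|---|---|---|---|
| Continuous efficacy | 4 | 1 − 0.8145 = 18.5% | 15.6% | 11.4% |
| All continuous | 6 | 1 − 0.7351 = 26.5% | 20.7% | 13.9% |
| All efficacy, if the threshold were extended | 8 | 1 − 0.6634 = 33.7% | 25.0% | 15.7% |
| All efficacy and safety, if the threshold were extended | 26 | 1 − 0.2635 = 73.6% | 47.5% | 24.5% |

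The first two rows rest on what the document fixes. The last two depend on a plan not yet written when the protocol was finalised. The expected number of false positives is 4 × 0.05 = 0.2 in the first row and 6 × 0.05 = 0.3 in the second.

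**Step 4: baseline tests.** After proper randomisation, any baseline difference between the arms is due to chance. A p-value on it tests something already known and cannot guide interpretation.

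**The case against.** The strongest reply is that 9.2 fixes little. Its threshold belongs to a paragraph about two tests for continuous data; 20 of 26 endpoints wait for a later plan that may well set multiplicity rules; and matters left to such a plan are not faults in a protocol. This stands as a limit on size. A reader might infer that every secondary is to be tested at 0.05 and quote 47.5%, but the text does not support that.

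Secondly, 18 of the 26 are safety endpoints, where unadjusted testing is usual because adjustment can hide harm. This also stands, and it is why the 4-endpoint figure is shown separately.

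Thirdly, three of the 4 continuous efficacy items are fluid measures close to the primary, and one is the primary with prehospital fluid added. Their correlation may be towards the high end, giving 11.4% rather than 15.6%. If guidance really changes the fluid given, those three are not true nulls and the family at risk is smaller. Most of the patient outcomes (organ failure, ICU admission, mortality) are in the deferred group.

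Lastly, the protocol promises no family-wise 5% and nowhere says that a secondary would establish success. That is fair: no stated error rate is broken.

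None of this removes the central point. The deferral does not mention multiplicity and does not withdraw the rule already set for continuous secondaries. That rule is a positive statement in the protocol, not a silence.

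**Conclusion.** The concern holds in a limited form. Section 9.2 allows a secondary result to be called significant at unadjusted 0.05 after a failed primary, and gives the efficacy and safety secondaries no order or supportive status. For the endpoints whose test and threshold are fixed, the chance of at least one false significant result is about 21% for all 6, or about 16% for the 4 efficacy ones. Even at a correlation of 0.8 the smaller family gives 11.4%, more than twice the per-test level. These figures assume that no endpoint is truly affected, that tests are two-sided, and that correlation is equal across endpoints; the correlation is an assumption, not a figure from the protocol.

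The 47.5% figure describes what would follow if the later plan copied the threshold to all 26 endpoints. It does not describe what the protocol now says.

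The mismatched mortality times, the double classification of time to vasopressor and the baseline p-values are smaller, separate defects. They do not enter the percentages but should be corrected in the same edit.

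**What to change.** In 9.2, replace the significance sentence with wording to this effect:

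> The primary endpoint is the only confirmatory test (two-sided 0.05). Secondary efficacy endpoints are supportive or exploratory. They are reported as estimates with 95% confidence intervals not adjusted for multiplicity, and no confirmatory claim will rest on an isolated p < 0.05. Safety endpoints are reported without adjustment and read as signals.

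If the sponsor wants a secondary claim, name a short ordered list now and test it in fixed sequence only if the primary is significant. New-onset organ failure as defined in 8.1.2 is a poor candidate: it counts vasopressor use as organ support, while the guided algorithm in 5.1 itself prescribes vasopressors.

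Then:

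- carry the same rule into the deferred plan for binary and time-to-event endpoints;
- use one set of mortality time points and one classification of time to vasopressor in sections 2 and 8.1.2;
- in 9.1, describe baseline characteristics by arm without p-values.

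The cost is wording only, with no extra patients or data, and the change is most credible before results are seen. The one small loss is that isolated p < 0.05 results on secondary efficacy endpoints can no longer be presented as established effects.
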